**WP-III**									
**Procedures**	**Antenatally**	**1st DoPL©**	**2nd DoPL©**	**Screening, consenting and data collection**					
				**T0**	**T1**	**T2**	**T3**	**T4**	**T5**
Screening and eligibility assessment	-	-	-	-	**√**	-	-	-	-
Initial conversation with the research team	-	-	-	-	**√**	-	-	-	-
Informed consent	-	-	-	-	**√**	-	-	-	-
Parents semi-structured interviews	-	-	-	-	-	-	**√**	-	-
Clinicians semi-structured interviews	-	-	-	-	-	-	-	-	**√**

© Day(s) of postnatal life (DoPL)

T0 = 5th DoPL

T1 = 9th DoPL

T2 = 10th DoPL

T3 = 10th–17th DoPL

T4 = 36 weeks of PMA or gestation in weeks if discharged home earlier than 36 weeks PMA

T5 = semi-structured interviews will be conducted within one month after obtaining consent

^a^If possible

### WP-1

#### Objectives

To assess the feasibility and acceptability of the study procedures (e.g. recruitment, echo scan performance, data collection, storage and analysis)To identify the sensitive echo parameters in assessing the RV function of the heart to be included in a prediction model to identify early BPD in premature infants

#### Study design and settings

This is a longitudinal, observational, cohort and feasibility study that will be conducted at the regional tertiary neonatal intensive care unit (NICU) at University Hospitals Plymouth NHS Trust (UHP), Plymouth.

#### Recruitment and sample size

The exploratory nature of this feasibility study sets a realistic target of recruiting 40 preterm infants who are born before 32 weeks of gestation.

The regional NICU at the UHP admitted 89, 101 and 69 preterm infants who were born before 32 weeks PMA in the years 2018, 2019 and 2020, respectively. Based on the careful examination of the admission data of 2018, two thirds of these preterm infants met the inclusion criteria of the proposed study, with one third of them developing moderate-to-severe BPD.

Therefore, the proposed feasibility study’s realistic sample size is 40 preterm infants over an 18-month recruitment period. Following are the participants whose data will be subjected to the trial analysis:Infants who survived until the gestational age when the diagnosis of no BPD or severe BPD can be establishedInfants who died before the set gestational age (36 weeks PMA) when severe BPD was identified as the main cause of death

The screening for potential recruits against the inclusion and exclusion criteria (Table 2) will be conducted at the following two timepoints:Timepoint 1: If possible, antenatal screening will be conducted by the clinical neonatal team by reviewing the maternal medical notes. Then, the neonatal research team will be informed so that the initial conversation can occur antenatally if the unborn infant is deemed a potential recruit.Timepoint 2: If screening is not possible antenatally, then parents of the suitable preterm infants will be approached in the second DAB of their children.

**Table 2 Tab2:** Inclusion and exclusion criteria for WP-I

Inclusion criteria	Exclusion criteria
1. Born at < 32 weeks gestational age. 2. The echo scans are indicated as per the recommended neonatal practice [19]: i. Preterm infants who require mechanical ventilation or non-invasive respiratory support (CPAP ≥ 4 cm H_2_O, high flow ≥ 4 L/min) ii. Detection of a cardiac murmur in the first 3 days after birth iii. Assessment of patent ductus arteriosus (PDA) iv. Preterm infants have central line in-situ, so echo is needed to assess line position	1. Preterm infants with major congenital anomalies, such as pulmonary hypoplasia or congenital heart disease (except PFO or PDA) 2. Preterm infants with a poor prospect of survival 3. Preterm infants whose parents do not consent 4. Preterm infants who are still in need of blood pressure supporting medications, such as, (inotropes) when the study echo scans are due 5. Preterm infants need inhaled nitric oxide gas when the study echo scans are due

*PDA* patent ductus arteriosus, *PFO* patent foramen ovale

All parents will be spoken to in person by the neonatal research team, who are also part of the neonatal clinical team in the antenatal wards in the delivery suite antenatally or in the neonatal unit postnatally. A clear verbal explanation will be provided about the trial and why the parents and their preterm infants are invited to participate. They will also be given a participant information sheet (PIS) and an informed consent form (ICF). If the parents wish for their preterm infant to be recruited for the study when feel well-informed and satisfied with the explanations provided, they will be asked to sign the ICF.

Consent will be sought for WP-I and WP-II from the parents of the eligible-for-inclusion preterm infants on the second DAB. All participants will be informed that they are free to withdraw from the study at any time without giving reasons and without prejudicing further treatment.

A delegation log will be maintained to ensure that the medical practitioners registered as study delegates participating in the consenting process of this study are duly authorised, have completed the Good Clinical Practice (GCP) training, are experienced clinicians and competent to participate according to the ethically approved protocol, principles of GCP and Declaration of Helsinki [20].

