The recent classifications of BPD divide the disease into grades I, II, III and/or III(A) according to its severity [12, 13]. These classifications [12, 13] include additional modalities of respiratory support, such as Humidified Heated High Flow Nasal Cannula, which was not included in the previous definition by Jobe and Bancalari [11]. Irrespective of the diagnostic definition used, the formal diagnosis and severity of BPD will not be established until the preterm infant is 36 weeks of PMA or at discharge (if the infant is discharged prior to that).

Czernik et al. [15] demonstrated a persistently elevated myocardial performance index of the RV in the first 2 weeks after birth (WABs) in preterm infants with incipient BPD. The identification of RV dysfunction associated with early BPD through echocardiography (echo) scan examination in these 2 weeks can serve as a marker for detecting preterm infants with the condition [15, 16].

The data obtained from 1735 infants born between 23 and 30 weeks of gestational age showed that the proportion of these infants needing oxygen decreases from birth to the 7th day after birth (DAB). This is followed by a steep rise in the number of infants requiring oxygen in the same cohort at the start of the second WAB [17]. These studies indicated that pathological pulmonary changes start as early as the first WAB [15, 17].

This paper describes the protocol of the proposed clinical study, which examines the applicability of RV functional assessment in an early BPD prediction model. This study protocol details three work packages (WPs): WP-I, which comprises the performance of two echo scans at the 5th and 9th DABs; WP-II, which is an embedded qualitative research project that aims to examine the parental perception of their participating preterm infants’ health; this is performed by analysing the parental written notes in the neonatal unit diary in the first 10 DABs; and WP-III, which is a further qualitative research project that involves conducting semi-structured interviews with 10–15 parents of the participating preterm infants and 10–15 health professionals who are involved in the initial phases of this study.

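### The analysis set keeps deaths before 36 weeks PMA only when blamed on severe BPD, so who is analysed depends on later events and an outcome-related judgement

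*Protocol article*

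**What the plan says.** In Methods, WP-1, Recruitment and sample size, the protocol article names the participants to be analysed. They are infants who live long enough for BPD status to be determined, and infants who die before 36 weeks PMA "when severe BPD was identified as the main cause of death". No other early death is listed.

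The Background states that "the formal diagnosis and severity of BPD will not be established until the preterm infant is 36 weeks of PMA", or at discharge if that comes earlier. Under Data collection and analysis there are two comparison groups, moderate or severe BPD and mild or no BPD. Neither is defined to include deaths. The model is to combine echo parameters with gestational age at birth and with oxygen and ventilatory support recorded at the scans.

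On timing, "Consent will be sought for WP-I and WP-II from the parents of the eligible-for-inclusion preterm infants on the second DAB", and the scans follow on days 5 and 9. Two exclusions in Table 2 are judged at the scans. Criterion 4 covers "Preterm infants who are still in need of blood pressure supporting medications, such as, (inotropes) when the study echo scans are due", and criterion 5 does the same for inhaled nitric oxide.

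**The concern.** A model meant for use at day 5 or day 9 should be developed in the infants who would be scanned then. Here some of them are removed because of what happens weeks later. The rule is also asymmetric: a death attributed to severe BPD is kept, and any other death is lost. Assigning that cause means judging the outcome itself, before the time at which the Background says severity is formally established. The article gives no criterion for doing so.

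The lost deaths may well bear on the question. The Background links BPD to a higher death rate, and severe BPD to pulmonary arterial hypertension with high mortality. The consequences reach beyond 40 infants: building the model is a key criterion for progression, the descriptive data will size the definitive study, and the Discussion plans a multi-centre test of the model.

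A smaller point concerns criteria 4 and 5. They act after consent, and the text does not say whether treatment at one scan removes that scan or the infant. Read per infant, treatment on day 9 would discard a usable day 5 scan, which is again selection on a later event.

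**Working it through.** **1. Timing.** Infants are born before 32 weeks, so 36 weeks PMA is more than 36 − 32 = 4 weeks (28 days) after birth. That is at least 28 − 9 = 19 days after the second scan. Survival to that point cannot be known when the predictors are measured.

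**2. Where each infant goes under the stated rules.**

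| Course after the scans | Place in the comparison |
|---|---|
| Reaches assessment, moderate or severe BPD | Case |
| Reaches assessment, mild or no BPD | Control |
| Dies before 36 weeks PMA, severe BPD judged the main cause | Can only be a case |
| Dies before 36 weeks PMA, any other cause | Not analysed |

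**3. The plan's own figures.** The target is stated as a "realistic sample size is 40 preterm infants over an 18-month recruitment period". No formula lies behind it. The unit "admitted 89, 101 and 69 preterm infants who were born before 32 weeks PMA in the years 2018, 2019 and 2020", and for 2018 "two thirds of these preterm infants met the inclusion criteria of the proposed study", "with one third of them developing moderate-to-severe BPD". Eligible infants over 18 months = annual admissions × 2/3 × 1.5:

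- 2018: 89 × 2/3 × 1.5 = 89, so 40 is 45% of the pool
- 2019: 101, so 40 is 40%
- 2020: 69, so 40 is 58%

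The target is plausible as recruitment, but no allowance for death is stated. Expected BPD cases are 40 × 1/3 = 13.3, provided all 40 reach assessment.

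**4. Effect of dropping deaths.** The article gives no death rate. Assume d = 2, 4 or 6 of 40 infants (5%, 10%, 15%) die before 36 weeks PMA of other causes, and that one third of the rest have moderate or severe BPD.

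- Analysed: N = 40 − d
- BPD cases: (40 − d)/3
- Death-or-BPD events: d + (40 − d)/3, out of 40

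| d | N analysed | BPD cases | Death-or-BPD events | Event rate in all 40 |
|---|---|---|---|---|
| 2 | 38 | 12.7 | 14.7 | 36.7% |
| 4 | 36 | 12.0 | 16.0 | 40.0% |
| 6 | 34 | 11.3 | 17.3 | 43.3% |

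The event rate thus moves 3.3 to 10.0 points above the 33.3% assumed in the analysed set. Adding d to 13.3 would be wrong, because it counts cases as if all 40 had survived.

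**5. Direction.** As an illustration only, assume a marker with SD 1 and means 0 (no BPD), 1 (BPD) and 1.5 (other deaths). With deaths dropped, AUC = Φ(1/√2) = 0.760. Deaths against no BPD give Φ(1.5/√2) = 0.856, and deaths as controls against BPD cases give Φ(−0.5/√2) = 0.362. Weighting by the numbers in step 4:

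- Deaths counted as events: 0.773, 0.784 and 0.793 for d = 2, 4 and 6. For d = 4: (12 × 0.760 + 4 × 0.856)/16 = 0.784.
- Deaths counted as non-events: 0.731, 0.703 and 0.677. For d = 4: (24 × 0.760 + 4 × 0.362)/28 = 0.703.

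The same infants move apparent discrimination up or down according to how death is handled.

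**The case against.** The aim is the right-ventricular burden of early BPD. Deaths from unrelated causes would blur that target, so making death-or-BPD the main outcome is a preference rather than a requirement. This stands, and it is why a second, prespecified analysis is enough.

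The Background speaks of a formal diagnosis, allows for discharge before 36 weeks, and mentions a 28-day point in the diagnostic definition. It also cites a grade III(A) that the article does not define. A full protocol may say how a BPD death is assigned. So the two sections are hard to square, but a flat contradiction is not proven. This does not answer the selection problem, which remains however well the cause is assigned.

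A reader might make three stronger inferences that the documents do not support:

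- *That criteria 4 and 5 bias the model by removing the sickest infants.* Need for such support is known when a scan is due, so the exclusion is largely a declared restriction of the population. It limits applicability. It becomes selection on a later event only if one day's treatment discards the other day's scan, and the text is silent on that. Nor are the sickest infants simply removed, since deaths attributed to severe BPD are kept.
- *That lost infants leave the progression denominators.* Criterion 1.3.3 in the Background refers to recruited infants, and recruitment and retention are separate outcomes. Nothing removes an infant from those rates.
- *That the bias has a known direction.* Step 5 shows that it has not.

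Finally, exclusion criterion 2 (poor prospect of survival) should lower deaths among those recruited, so the assumed 2 to 6 may be too high.

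**Conclusion.** The point holds for the death rule. As written, inclusion depends on survival unknown at scan time and on a cause-of-death judgement linked to the outcome. Early deaths can enter only as cases, and the others have no place in the comparison. The model can therefore be biased for the infants it would be used on.

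The size is not computable from the article. The contrast of 14.7 to 17.3 events with 11.3 to 12.7 cases rests on two assumptions: 2 to 6 other-cause deaths in 40, and one third BPD among the rest. On criteria 4 and 5, only the unstated unit, scan or infant, needs settling. In a 40-infant feasibility study this should be corrected mainly because the model and its rates feed the definitive study.

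**What to change.** 1. Replace the cause-of-death test with a rule that accounts for every consented infant with at least one analysable scan.
2. Report the comparison of moderate or severe with mild or no BPD in infants who reach assessment. Beside it, report a prespecified analysis that counts death from any cause before 36 weeks PMA together with moderate or severe BPD.
3. State that criteria 4 and 5 are applied per scan in the analysis, so that a usable scan from the other day and the 36-week outcome are kept.
4. Report deaths, scan-level exclusions and other losses, with reasons, against the number recruited.

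The cost is a change of wording, 36-week outcomes for possibly a few more infants, and one added analysis. The downside is that the added analysis has a mixed outcome, so it should be read beside the BPD comparison and not in place of it.

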**WP-I and WP-II**									
**Procedures**	**Antenatally**	**1st DoPL©**	**2nd DoPL©**	**Data collection**					
				**T0**	**T1**	**T2**	**T3**	**T4**	**T5**
Screening and eligibility assessment	**√**^a^	**√**	-	-	-	-	-	-	-
Initial conversation with the research team	**√**^a^	-	**√**	-	-	-	-	-	-
Informed consent	-	-	**√**	-	-	-	-	-	-
Demographics (when consent obtained)	-	-	**√**	-	-	-	-	-	-
Echo scan on 5th DoPL	-	-	-	**√**	-	-	-	-	-
Echo scan on 9th DoPL	-	-	-		**√**	-	-	-	-
Working weight	-	-	-	**√**	**√**	-	-	-	-
Vital signs including systolic, diastolic, and mean Blood Pressure (BP)	-	-	-	**√**	**√**	-	-	-	-
Collection of NICU parents/patients’ diary copies	-	-	-	-	-	**√**	-	-	-
Collection of data related to outcomes/diagnosis of BPD	-	-	-	-	-	-	-	**√**	-

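### Screening and consent are scheduled to finish by day 2, but an infant can first qualify on day 3 and the first scan is on day 5, so late qualifiers have no route to enrolment

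*Protocol article*

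**What the plan says.** **Screening.** In Table 1 (WP-I and WP-II) the row "Screening and eligibility assessment" is ticked antenatally, if possible, and on the 1st day of postnatal life, with dashes from the 2nd day on. The text under WP-1, Recruitment and sample size, differs slightly. It names two screening timepoints, and the second is day 2: "If screening is not possible antenatally, then parents of the suitable preterm infants will be approached in the second DAB of their children".

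**Consent.** In Table 1 the row "Informed consent" is ticked on the 2nd day only. The text below Table 2 says the same: "Consent will be sought for WP-I and WP-II from the parents of the eligible-for-inclusion preterm infants on the second DAB". WP-II, Data collection and analysis, also takes consent as given on day 2, hands out the diary then, and collects entries from day 2 to day 10.

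**Eligibility.** Table 2 requires a clinical indication for the scan. One indication is "Detection of a cardiac murmur in the first 3 days after birth". The other three carry no day limit: "Preterm infants who require mechanical ventilation or non-invasive respiratory support" (with stated thresholds), assessment of the ductus, and a central line in place.

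**First study procedure on the infant.** The Table 1 row "Echo scan on 5th DoPL" is the first scan; the second is on day 9.

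**Use of the recruitment rate.** Recruitment and retention rates are secondary outcome 1.2.3, and satisfactory recruitment is progression criterion 1.3.2. Table 3 lists the suitability of the eligibility criteria as a WP-I outcome. The article states no denominator for the recruitment rate.

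**The concern.** The eligibility criteria and the enrolment schedule run on different clocks. A criterion that can first be met on day 3 cannot be applied by a schedule whose last screening point is day 1 (Table 1) or day 2 (text) and whose only consent point is day 2. The same schedule gives no later day to parents who are not available, or have not decided, on day 2. Where there was no antenatal contact, Table 1 places the first conversation and the consent on that same day.

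Two things are at stake. Accrual towards 40 infants may be slower than the eligible pool allows. And the recruitment rate, which feeds the decision to proceed to a definitive study, would reflect what can be achieved on one day rather than in the whole population that Table 2 defines.

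**Working it through.** **Step 1: follow an infant through the schedule.**

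| Infant | Meets Table 2? | Screening point? | Consent point? |
|---|---|---|---|
| On respiratory support or with a central line by day 1 | Yes | Yes | Day 2 |
| Only indication is a murmur found on day 2 | Yes | Not in Table 1; possibly under Timepoint 2 in the text | Day 2, if found in time |
| Only indication is a murmur found on day 3 | Yes | None | None |
| Indication i, iii or iv first arises on day 3 or 4 | Yes (no day limit stated) | None | None |
| Qualifies on day 1, parents absent or undecided on day 2 | Yes | Yes | None after day 2 |

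The last three rows are the gap. Nothing in the article provides for screening or consent between day 2 and the scan on day 5.

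**Step 2: the accrual base.** The target of 40 is a pragmatic one. The article gives no uptake rate, so 40 cannot be re-derived; what can be derived is the uptake it implies. Inputs, all from Recruitment and sample size: admissions below 32 weeks of 89 (2018), 101 (2019) and 69 (2020); two thirds eligible; 18 months.

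Eligible in 18 months = admissions × 2/3 × 1.5, which equals the yearly admissions.

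- 2018: 89 × 2/3 × 1.5 = 89; uptake needed 40/89 = 44.9%
- 2019: 101 × 2/3 × 1.5 = 101; 40/101 = 39.6%
- 2020: 69 × 2/3 × 1.5 = 69; 40/69 = 58.0%
- Mean: (89 + 101 + 69)/3 = 86.3; 40/86.3 = 46.3%

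**Step 3: sensitivity to late qualification.** Let f be the share of eligible infants who first qualify after the window closes. The documents do not give f; 2% to 20% is an assumption. At the mean of 86.3 eligible infants, reachable = 86.3 × (1 − f) and uptake needed = 40/reachable.

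| f | Reachable | Uptake needed |
|---|---|---|
| 2% | 84.6 | 47.3% |
| 5% | 82.0 | 48.8% |
| 10% | 77.7 | 51.5% |
| 20% | 69.1 | 57.9% |

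At f = 20% the range over the three years is 49.5% (40/80.8) to 72.5% (40/55.2). The target stays arithmetically reachable throughout.

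**Step 4: what happens to the recruitment rate.** Take an illustrative uptake of 50% among infants reached.

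- Recruited over infants screened as eligible: 50% for every f, because late qualifiers are in neither numerator nor denominator.
- Recruited over all infants ever eligible: 50% × (1 − f) = 49%, 47.5%, 45% and 40% at f = 2%, 5%, 10% and 20%.

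Families screened in time but not reached or not decided on day 2 are a separate group. They count in either denominator and are not recruited, so they lower the rate relative to a longer window. The article gives no figure for them.

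**The case against.** **Day 2 has a purpose.** Consent covers WP-I and WP-II together, and WP-II studies parents' notes over the first 10 days, with the diary handed out at consent. A reader might infer that nothing in the design calls for early consent; WP-II shows otherwise. This stands. It supports day 2 as the usual day but does not require excluding those who come later.

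**Day 2 only is an inference.** The text says when consent will be sought and does not forbid a later signature. Parents are asked to sign once they feel informed, and the full protocol may deal with late consent. This stands in part. But Table 1 and two parts of the text agree on day 2, and no part of the article gives another day.

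**The indications read as alternatives.** An infant already on respiratory support or with a central line is not lost when a murmur appears later. This stands and limits the likely loss.

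**A feasibility study exists to find such problems.** Outcome 1.2.2 asks whether screening and recruitment need adjusting, and WP-III explores recruitment. This stands only in part. With no screening scheduled after day 2, late qualifiers need never be logged, and WP-III interviews only parents whose infants were recruited.

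**Stronger readings that the documents do not support.** A reader might infer that the recruitment rate is biased low. Step 4 shows that, for late qualifiers, this depends on a denominator the article does not state; over all eligible infants, the lower rate correctly describes this procedure. A reader might also suppose that weekend staffing or late transfers into the unit make the loss large. The article gives no staffing limit and no transfer figures, and it says the research team are also part of the clinical team.

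**Conclusion.** The mismatch is real and comes from the article's own text. An infant whose only indication is a murmur found on day 3 meets Table 2 but has no screening or consent point. The same is true of consent for families not reached or not decided on day 2. Table 1 and the text also disagree on whether the last screening point is day 1 or day 2.

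The size is unknown and may be small. The uptake needed for 40 is 39.6% to 58.0% on the three years of admissions, assuming that the two-thirds eligible share, which was taken from 2018, holds in each year. A loss of 2% to 20%, itself an assumption, makes the target harder but not unattainable. What can be concluded is that accrual may be lower than it need be, and that the rate used for outcome 1.2.3 and criterion 1.3.2 will describe a one-day window rather than the eligible population. A downward bias of known size, or a cohort skewed towards particular families, is not shown.

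**What to change.** 1. In Table 1, in Recruitment and sample size (Timepoint 2 and the consent paragraph below Table 2), and in WP-II, Data collection and analysis, keep day 2 as the usual consent day and allow screening and consent at any time before the day 5 scan. This makes criterion 2.ii workable and removes the disagreement over the last screening day.
2. Give the diary at consent and record the day it starts, so that WP-II can take account of shorter records.
3. Report the recruitment rate over all infants who meet the criteria before the day 5 scan, and log those who qualify after day 2.

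The cost is a wording change in those places and a few more days of screening per infant. Consent as late as day 5 would give a diary of days 5 to 10 (6 days) instead of days 2 to 10 (9 days), up to 3 days shorter. Under the present schedule those families would contribute no diary at all.
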